## **6.3 Summary of findings from non-clinical studies**

### *Anaerobutyricum soehngenii*

In obese mice, *A. soehngenii* treatment improved insulin sensitivity and reduced intrahepatic triglyceride content. *A. soehngenii* is well known to not only convert sugars but also lactate and acetate into butyrate. This latter SCFA may protect against NASH. Butyrate may reduce the inflammatory component of NAFLD by promoting differentiation

of regulatory T cells. It also has an anti-migratory effects on neutrophils, and in the gut, it protects epithelial barrier integrity, both potentially protective effects on NASH. Moreover, lactate is found to be increased in T2DM; the efficient conversion of lactate into butyrate by *A. soehngenii* is expected to contribute to its beneficial actions.

#### *Bifidobacterium animalis*, subsp. *lactis*

In this context, the role of *B. animalis* subsp. *lactis* is important to note as the well-studied strain BLC1 is marketed as a probiotic and well characterized. Via cross-feeding it can form a trophic chain with *A. soehngenii*. Fermenting FOS, *B. animalis* subsp. *lactis* can produce lactate and acetate, which *A. soehngenii* uses to produce butyrate. This is, moreover, shown in in vitro studies of a model of the small intestine (Deyaert et al 2022, in preparation).

#### *Akkermansia muciniphila*

Pasteurized *A. muciniphila* is involved in host immunological homeostasis at the gut mucosa, improvement of gut barrier function and contributes to metabolic health. In a study assessing the effects of pasteurized *A. muciniphila* on diet-induced metabolic disorders in mice, it was not only found that pasteurization did not diminish the beneficial effects, but it also unexpectedly enhanced the beneficial impact of *A. muciniphila*. A recent study in a high fat induced fatty liver mouse model showed that administration of *A. muciniphila* cells prevented fatty liver disease by regulation of the expression of genes that regulate fat synthesis and inflammation in the liver. In both earlier mice and human studies it was found that pasteurized *A. muciniphila* cells were similar or more efficient than the same amount of live *A. muciniphila* cells.

## 6.4 Summary of findings from clinical studies

### *Allogenic Lyophilized Fecal Microbiota Transplantation (LFMT) capsules*

We recently published the first vegan fecal microbiota transplantation study in patients with NASH and aberrant microbial composition. This pilot study found anti-inflammatory effects of vegan FMT into NASH patients, with a trend towards reduced hepatic necro-inflammation. Although the exact mechanism is not well understood, the key hypothesis is that the microbiota of vegan donors consist of more butyrate producers and less gram negative lactate producers. By transplanting (and thus replacing) the microbiota, more butyrate (and less lactate) is produced in the intestines.

The current study will use LFMT capsules instead of (more traditional) fresh FMT administered per nasoduodenal tube, The first notion of LFMT capsules stems from 2015,

when Tian et al. effectively treated 1 rCDI patient with 5 LFMT capsules for two consecutive days. Next, Hecker et al. treated 20 rCDI patients with LFMT capsules, which resulted in successful resolution of diarrhea in 17 (85%) patients. These findings were reproduced three other prospective cohort studies reporting successful resolution of CDI in 43/49 (88%), 28/32 (88%) and 33/37 (89%) of patients. The first RCT in which LFMT capsules were compared to frozen FMT via enema as treatment for rCDI was conducted in 2018 by Jiang et al. This study showed an equal efficacy for both the LFMT and frozen FMT products, with 26/31 (84%) and 30/34% (88%) of patients achieving resolution of rCDI, respectively. In addition, authors did not find any differences in adverse events between both groups. Finally, one RCT has been published comparing LFMT capsules to placebo for treatment of small intestinal bacterial overgrowth. After taking LFMT capsules once a week for four consecutive weeks, gastrointestinal symptoms significantly improved and gut microbiota diversity significantly increased compared to the placebo group.

In addition to a comparable efficacy of LFMT capsules with fresh FMT, above studies showed oral treatment with capsules is relatively simple, well tolerated and safe. Adverse events were limited to minor gastrointestinal symptoms and comparable to fresh FMT. The most commonly reported adverse experiences are gastrointestinal symptoms, including abdominal pain, fecal urgency, nausea, diarrhoea and flatulence. In addition, like fresh FMT, the lyophilized microbiota was able to increase bacterial diversity and shift the microbiota composition towards a donor profile, which was observed up to one year following LFMT treatment.

Besides above-mentioned studies with LFMT capsules, multiple studies have been performed with capsules containing a frozen FMT suspension. Among these, FMT capsules have been used to treat irritable bowel syndrome, hepatic encephalopathy, metabolic syndrome and obesity. Finally, capsules containing a frozen autologous fecal suspension have been tested as a supplement to successfully prevent weight regain after a lifestyle intervention. Like the LFMT capsules, these capsules were found to be well tolerated, safe and effective. Although the formulation and processing is different within most studies, these studies show that the fecal transplant remains viable and able positively influence the recipients' intestinal microbiome.

#### *Anaerobutyricum soehngenii*

The pilot study also showed that upon vegan FMT engraftment, the gut microbiome of the NASH patients was enriched in *Anaerobutyricum soehngenii* and other butyrate-producing Lachnospiraceae. Furthermore, in obese mice, *A. soehngenii* treatment improved insulin sensitivity and reduced intrahepatic triglyceride content. *A. soehngenii* is well known to

not only convert sugars but also lactate and acetate into butyrate. As previously stated, this latter short chain fatty acid may protect against NASH. Butyrate may reduce the inflammatory component of NAFLD by promoting differentiation of regulatory T cells. It also has an anti-migratory effects on neutrophils, and in the gut, it protects epithelial barrier integrity, both potentially protective effects on NASH. Moreover, lactate is found to be increased in T2DM; the efficient conversion of lactate into butyrate by *A. soehngenii* is expected to contribute to its beneficial actions.

#### *Bifidobacterium animalis* subsp. *lactis* BLC1

Bacterium *Bifidobacterium animalis* subsp. *lactis* BB12 is arguably the most studied probiotic bacterium. It's potential role in many conditions, varying from dental caries to infant colic and metabolic syndrome has been studied. Some studies also addressed its potential role application in NAFLD. The majority of these studies involved the use of additional bacteria.

The strain that is used for the SYNCH study is *Bifidobacterium animalis* subsp. *lactis* BLC1, the closest relative of BB12, showing 99,9% sequence identity at the nucleotide level.

#### *Akkermansia muciniphila*

A randomized, double-blind, placebo-controlled proof-of-concept study in overweight/obese insulin-resistant human volunteers showed that the daily supplementation with pasteurized *A. muciniphila* for 12 weeks improved several metabolic parameters such as insulin sensitivity, insulinemia, plasma total cholesterol, as well as relevant blood markers for liver dysfunction and inflammation while serum lipopolysaccharide levels were decreased, indicative of improved barrier function.

## 6.5 Summary of known and potential risks and benefits

### *Allogenic Lyophilized Fecal Microbiota Transplantation (LFMT) capsules*

FMT is a well-studied and safe procedure. Previous studies with LFMT capsules have indicated no procedure-related serious adverse events after treatment with LFMT capsules and only minor gastrointestinal symptoms were reported by participants. These gastrointestinal symptoms consisted mainly of abdominal pain, fecal urgency, nausea, diarrhoea and flatulence, and were similar in the placebo group.

One potential adverse event with FMT delivered via the upper gastrointestinal route, is the risk of FMT reflux into the stomach. To date, no such events have been reported after ingestion of LFMT capsules. To mitigate this risk, the LFMT is encapsulated in NGE

capsules, which will not disintegrate until they have passed the stomach. In addition, the ingestion of the bulk of 21 capsules is spread evenly over the day, so that the capsules will not clot together in the stomach (impairing passage) and reducing the chance of nausea and vomiting. In comparison, the daily ingestion of 25 capsules for 3 consecutive days was well tolerated in a study with irritable bowel patients, without serious adverse events.

#### *Pre- and probiotics*

*Anaerobutyricum soehngenii* and *Bifidobacterium animalis*, subsp. *lactis* are commensal inhabitants of the human intestine, and safe to administer. Pasteurized *A. muciniphila* is a pasteurized form of another commensal of the gut, and safe to administer in humans. The combination of these 3 bacteria is not well studied, although we expect no negative effect of interbacterial actions.

Fructo-oligosaccharides are indigestible prebiotics, which are safe and over-the-counter available.

### **6.6 Description and justification of route of administration and dosage**

FMT or placebo will be given per orally per capsule. All bacterial strains and FOS will be ingested orally per capsule. The dosage of  $10^9$  *A. soehngenii* CH-106 cells is based on previous studies and safety study (provided by Caelus Health). The dosage of  $10^{10}$  *B. animalis* subsp. *lactis* is widely recognized and used. The dosage of  $3 \times 10^{10}$  pasteurized *A. muciniphila* cells is based on safety and efficacy studies (provided by A-Mansia Biotech).

### **6.7 Dosages, dosage modifications and method of administration**

#### *Allogenic Lyophilized Fecal Microbiota Transplantation (LFMT) capsules*

One LFMT capsule will contain approximately 235mg of lyophilized feces. This equals the bacterial load of approximately 750mg fresh feces, or 1500mg of fresh FMT. Depending on the fecal matrix and the water content, this might be slightly more or less. The dosage of the capsules will consist of 3 times a loading dose, and a maintenance dose. The loading dose will be 21 capsules on 1 day, ingested at the study visits. The maintenance dose will consist of the ingestion of 2 capsules daily for 24 weeks. The loading doses and the maintenance dose together equal the amount of 100 grams of fresh FMT administered every 8 weeks.

Capsules are to be ingested with a glass of water on an empty stomach in the morning, preferably an hour before breakfast (while still fasted). Patients store the LFMT capsules at home in a freezer, but can let the capsules warm to room temperature before ingestion.

#### *Pre- and Probiotics*

*Anaerobutyricum soehngenii* CH106 is given orally per capsule in a dosage of approximately  $\geq 1 \times 10^9$  live bacterial cells. *Bifidobacterium animalis* subsp. *Lactis* BLC1 is given orally per capsule in a dosage of around  $\geq 1 \times 10^{10}$  live bacterial cells. Pasteurized *Akkermansia muciniphila* MucT is given orally per capsule in a dosage of around  $3 \times 10^{10}$  pasteurized bacterial cells. Fructo-oligosaccharides are given orally as a powder in a dosage of 5 grams, once a day.

### **6.8 Preparation and labelling of Investigational Medicinal Product**

#### *Allogenic Lyophilized Fecal Microbiota Transplantation (LFMT) capsules*

Feces donors deliver their fresh feces cooled to the investigator at the AMC. The autologous feces are directly processed, whereby the feces are homogenized 1:1 with a lyoprotectant solution (10% trehalose and 5% maltodextrin in sterile saline, all pharmaceutical grade). Thereafter, the fecal suspension is filtered through double non-woven gauzes in a metal funnel (sterile) to remove any particulate matter. The resulting FMT is transferred to sterile flasks, 50 ml/flask, and frozen at  $-80^{\circ}\text{C}$ . Next, the flasks with frozen FMT are placed in the drying chamber of a freeze-dryer (Zirbus VaCo 2) and lyophilized during 48 hours. The resulting lyophilized FMT is subsequently transferred to a mortar, ground to a fine powder and mixed with lubricant (silicon dioxide, pharmaceutical grade) to improve the flowing properties of the powder. If necessary, filler is added to the powder mixture (microcrystalline cellulose, pharmaceutical grade) to reach the necessary volume for the number of capsules to be filled. Finally, the LFMT powder is encapsulated in capsules with stomach acid resistant properties (NGE-caps, Capsugel). LFMT capsules are filled in opaque HDPE 50 ml containers (DUMA Twist-off), 28 capsules per container. Containers are labelled according to GMP-annex 13 and stored in a freezer at  $-80^{\circ}\text{C}$ .

The image below shows a schematic overview of the preparation to the LFMT capsules.

[figure not shown]

Figure 7: Overview of the production of LFMT capsules.

The label of the LFMT capsules will contain:

- the name of the study: the SYNCH-trial
- the Participant Number
- the Sponsor name
- the investigators name and contact details
- For investigational use only
- LFM-capsules.
- Contains: Bevat freeze-dried feces, natriumchloride, trehalose, maltodextrin and colloidal silicium dioxide.
- the Batch Number and the Expiry Date
- Storage conditions: Store at room temperature (-20 to -4°C), in a dry place away from direct sunlight – Keep away from children
- Instructions for use: Consume two caps per day, 15 minutes before breakfast with a glass of water.
- Emergency Contact Number
- Amsterdam UMCs address.

All labels of the bacterial strains and the FOS will contain:

- the name of the study: the SYNCH-trial
- the Participant Number
- the Sponsor name
- the investigators name and contact details
- For investigational use only
- Type of probiotic
- the Batch Number and the Expiry Date
- Storage conditions: Store at room temperature (15-25°C), in a dry place away from direct sunlight – Keep away from children
- Instructions for use: Consume one caps per day, 15 minutes before breakfast with a glass of water
- Emergency Contact Number
- Company name of the supplier.

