Throughout the study period, the participants will, in addition to the LFMT or placebo capsules, take the 3 bacterial strains in the morning combined with FOS. They will further be asked to retain their usual dietary habits during the study and to keep a nutritional diary from week -1 to 24 to monitor caloric intake including total calories, dietary carbohydrates, fat, proteins, and fibers. Blood pressure, body weight, and changes in health status will be documented.

Interventions: From the day of the first LFMT capsules until completion of the study, all participants will receive an oral daily dose of 5 grams of fructo-oligosaccharides [Sensus, Roosendaal]. Subsequently, participants will be randomized to receive lean donor LFMT or placebo capsules. This consists of 21 capsules at the first 3 study visits, and a daily ingestion of 2 capsules during the duration of the study (24 weeks). Placebo capsules will consist of saline with a brown pigment. During the 24 week study duration, all participants will also daily take  $10^9$  *A. soehngenii* CH-106 cells (dosage based on previous studies and safety study; provided by Caelus Health),  $10^{10}$  *B. animalis* subsp. *lactis* BLC1 (commercially available Sacco SRL) and  $3 \times 10^{10}$  pasteurized *A. muciniphila* cells (provided by A-Mansia Biotech), and 5 grams of FOS. We have previously observed that gut microbiota composition in the recipient is affected up to 8-12 weeks after donor FMT, so this time window ensures a stable donor gut microbiota composition during the study. The fecal donor samples will be collected, lyophilized ('freeze-dried'), encapsulated and stored at -80°C (see also paragraph 6.8). At home, participants will store the LFMT capsules in the freezer (-20°C). See figure 6 below.

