### *Anaerobutyricum soehngenii CH106*

Capsulated formulation of *A. soehngenii* CH106 will be delivered by Caelus in small bottles, each containing 50 capsules and a small silicabag to ensure low moisture inside the bottles. The sponsor will be responsible for storing *Anaerobutyricum soehngenii* CH106 in a proper place, inaccessible to unauthorized persons. The sponsor will be responsible for storing pAkk at the appropriate conditions and inaccessible to unauthorized persons.

The investigator agrees that *Anaerobutyricum soehngenii* CH106 will be dispensed only to study participants who have provided written consent. Participants will be instructed to store the product at room temperature (15-25°C), in a dry place away from direct sunlight.

*Bifidobacterium animalis subsp. lactis BLC1*

Capsulated formulation of *B. animalis* subsp. *lactis* BLC1, produced by SynBiotec will be delivered by Caelus. Further details can be provided upon delivery.

The sponsor will be responsible for storing *Bifidobacterium animalis subsp. lactis BLC1* in a proper place, inaccessible to unauthorized persons. The sponsor will be responsible for storing pAkk at the appropriate conditions and inaccessible to unauthorized persons.

The investigator agrees that *Bifidobacterium animalis subsp. lactis BLC1* will be dispensed only to study participants who have provided written consent. Participants will be instructed to store the product at room temperature (15-25°C), in a dry place away from direct sunlight.

*Pasteurized Akkermansia muciniphila MucT*

Pasteurized *Akkermansia muciniphila* will be provided to the sponsor by A-Mansia biotech. Production, packaging and labeling of pAkk will be performed by A-Mansia Biotech.

The sponsor will be responsible for storing pAkk in a proper place, inaccessible to unauthorized persons. The sponsor will be responsible for storing pAkk at the appropriate conditions and inaccessible to unauthorized persons.

The investigator agrees that pAkk will be dispensed only to study participants who have provided written consent. Participants will be instructed to store the product at room temperature (15-25°C), in a dry place away from direct sunlight.

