#### **7.6 Preparation and labelling of Non Investigational Medicinal Product**

The Frutalose® OFP powder will be supplied by Sensus, Roosendaal, in a 40 or 60 kg bag with a Certificate of Analysis to UAMC or the co-packer of choice for packing into sachets or tubs with scoops. Information will be provided by Sensus to facilitate the packing and labelling process as required.

- Product name: Frutalose® OFP
- Product Sponsor: Sensus BV provides the oligofructose as a gift to UMCA.
- Product Manufacturer: Sensus BV and co-packer (for tubs/ sachets)
- Active compound: oligofructose (fructo-oligosaccharides or oligo-saccharides)
- Formulation: Frutalose® OFP contains  $92 \pm 2\%$  oligofructose. Oligofructose is a polydisperse mixture of linear fructose polymers partly ended by a glucose molecule, coupled by means of  $\beta(2-1)$  bonds; it comprises a polydisperse mixture of linear fructose oligomers with degree of polymerization ranging between 2 and 10 units.
- Powder of 5 g sachet to be ingested at same time daily after sprinkling on or mixed in foods (e.g. breakfast cereal/ porridge/ yoghurt) or drinks (e.g. coffee/ tea). Fresh orange juice is possible too provided immediately consumed after mixing. Soft drinks are not suitable due to very low pH. Powder will be delivered in sachets or in containers with a 5 gram scoop.

- If the participant misses a dose in the morning, they can continue to take the missed dose later in the day (before meal). Participants should resume the normal instruction on the following day and missed doses should not be moved to the following day.

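### The LFMT capsule label in section 6.8 calls a sub-zero range room temperature, contradicting itself and the home freezer storage stated elsewhere in the protocol

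*Protocol*

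**What the plan says.** Section 6.8 sets out what the LFMT label will contain. Its storage line reads "Storage conditions: Store at room temperature (-20 to -4°C), in a dry place away from direct sunlight".

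The same section then gives one label list for the three probiotic strains and the fructo-oligosaccharides (FOS). There the storage line is "Storage conditions: Store at room temperature (15-25°C), in a dry place away from direct sunlight". Section 6.9 uses the same range for the probiotics: "Participants will be instructed to store the product at room temperature (15-25°C), in a dry place away from direct sunlight".

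Two other sections describe how participants keep the LFMT capsules at home:

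- Section 3: "At home, participants will store the LFMT capsules in the freezer (-20°C"
- Section 6.7: "Patients store the LFMT capsules at home in a freezer, but can let the capsules warm to room temperature before ingestion"

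On FOS, the shared list is introduced with "All labels of the bacterial strains and the FOS will contain" and includes "Instructions for use: Consume one caps per day, 15 minutes before breakfast with a glass of water". Section 7.6 describes FOS differently: "Powder of 5 g sachet to be ingested at same time daily after sprinkling on or mixed in foods".

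**The concern.** A label that names room temperature and a sub-zero range in the same line gives two incompatible instructions. A participant is more likely to act on the label than on sections 3 and 6.7. The strain and FOS labels carry the same storage sentence with only the bracketed range changed, so that range is all that distinguishes the one product meant for the freezer.

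LFMT versus placebo is the only treatment difference between the arms, and most of the course is the daily maintenance dose. If LFMT capsules were kept at room temperature for weeks, the active arm might not receive the product that the protocol intends. That possibility is the reason to correct the text. The documents do not show that it has happened or would happen.

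**Working it through.** This is a comparison of texts, and there is no sample size, power or alpha figure to reproduce.

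**Inputs**

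- LFMT label (section 6.8): the words room temperature, with the range -20 to -4°C.
- Room temperature elsewhere (strain and FOS label in section 6.8; probiotic storage in section 6.9): 15 to 25°C.
- LFMT at home (section 3): freezer, -20°C.
- LFMT at home (section 6.7): freezer, with warming to room temperature allowed only before ingestion.
- LFMT at the site (section 6.8): labelled containers in a freezer at -80°C.

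**Do the words fit the range?** No. The two ranges do not overlap, and the gap between their nearest limits is 15 - (-4) = 19°C.

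**Do the words fit home storage?** No. Against the section 3 setting, room temperature is warmer by 15 - (-20) = 35°C to 25 - (-20) = 45°C. Section 6.7 also treats room temperature as a separate state from storage.

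**Does the range fit home storage?** Yes. It lies wholly below zero and includes -20°C. Its upper limit is looser than the section 3 figure by -4 - (-20) = 16°C, but that is a difference in tolerance and not a contradiction. The faulty element is therefore the phrase room temperature.

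**Is the line current?** Yes. Section 14.1 records that the LFMT label was changed in the first amendment, and the line quoted from section 6.8 is in the present body text.

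**How much of the course is maintenance dosing?** Section 6.7 gives two capsules daily for 24 weeks (168 days) plus three loading doses of 21.

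- Maintenance on every day: 2 × 168 = 336; loading: 3 × 21 = 63; total 399; 336/399 = 84%.
- Maintenance on all days except the three loading days, as in section 6.2: 2 × 165 = 330; total 393; 330/393 = 84%.

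About 84% of the capsules are thus maintenance doses. The dispensing schedule is not stated. With visits 8 weeks apart, home storage for several weeks is likely if dispensing follows the visits.

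**The case against.** The strongest reply is that this is one wrong phrase. Deleting it removes every conflict listed above. The range on the label already fits a freezer, and sections 3 and 6.7 are clear, so staff preparing the label can see what was meant. The phrase may simply be left over from the near-identical strain label. No consequence is shown, no statistical quantity is affected, and the final printed label is not available. The temperature differences describe the text and measure no harm. On the upper limit, -20°C lies inside -20 to -4°C, a label may state a permitted range, and nothing in the documents shows that -4°C is too warm. The FOS slip is a separate clerical matter, since section 7.6 has it right.

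Most of this stands. It is a wording error, the upper limit is a minor point, and the FOS slip adds no weight to the main one. What does not follow is that the line can be left alone. Section 6.8 specifies what the label will contain, and the label is what participants have at home. Clear text in sections 3 and 6.7 helps staff but does not reach a participant reading the container.

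**Conclusion.** The concern holds. As written, the LFMT label contradicts itself, the 15-25°C that the protocol uses for room temperature, and the home freezer storage in sections 3 and 6.7. The error lies in two words, and the sub-zero range is consistent with the intended storage. The point should be corrected because it is a participant-facing instruction for the only product that differs between the arms.

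Its size is limited. It does not touch the design, the sample size or the analysis. Any effect on capsule viability or histological response cannot be computed from the documents and is not claimed. The conclusion assumes that the label follows section 6.8 as written; the printed label and the instructions given at dispensing have not been seen.

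**What to change.** In section 6.8, replace the LFMT storage line with: Store in a freezer (-20°C). This matches section 3. If the sponsor has data supporting storage up to -4°C, a range could be kept, provided that section 3 and the label state the same one. Check any labels already printed, and the dispensing instructions, against the corrected text.

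At the same time, take FOS out of the shared list that prescribes one capsule a day and give it the 5 g powder instruction from section 7.6.

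The cost is label text only. Visits, sample size and analysis are unchanged.
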